## Abstract

**Background:**

Polyphenols have been shown to be effective against many chronic diseases, including neurodegenerative diseases. Specifically, the consumption of raisins, being a food rich in polyphenols, has been attributed with neuroprotective benefits. Therefore, our main objective is to evaluate the effect of including 50 g of raisins in the diet daily for 6 months, on the improvement of cognitive performance, cardiovascular risk factors and markers of inflammation in a population of older adults without cognitive impairment.

**Methods:**

Design and intervention: This study will be a randomized controlled clinical trial of two parallel groups. Each subject included in the study will be randomly assigned to one of two study groups: control group (no supplement), intervention group (50 g of raisins daily during 6 months).

Study population: The participants will be selected by consecutive sampling in the Primary Care consultations of urban health centers in Salamanca and Zamora (Spain), taking into account the selection criteria.

Study variables: Two visits will be made, baseline and at 6 months. Cognitive performance will be evaluated (Mini-Mental State Examination test, Rey Auditory Verbal Learning Test, verbal fluency and montreal cognitive assessment (Moca)). It will also be analyzed the level of physical activity, quality of life, activities of daily living, energy and nutritional composition of the diet, body composition, blood pressure, heart rate, markers of inflammation and other laboratory tests of clinical relevance (glycaemia, total cholesterol, HDL cholesterol, LDL cholesterol and triglycerides). In addition, sociodemographic data, personal and family history, medication use and alcohol and tobacco consumption will be collected.

**Discussion:**

In this project, it is intended to contribute to minimize the problems derived from cognitive deterioration in older people.

**Trial registration:**

ClincalTrials.gov Identifier: NCT04966455 Registration date: July 1, 2021.

## Background

According to the World Health Organziation, between 2015 and 2050 the world population over 60 years of age will increase from 900 million to 2 billion, which represents an increase of 12 to 22% [1]. Due to the increase in longevity, the prevalence of neurodegenerative diseases and consequently cognitive impairment and dementia, are increasing exponentially in recent years.

Dementia is not part of normal aging, it is a disease that involves the deterioration of memory, intellect, behavior and the ability to perform activities of daily living. It is one of the main causes of disability and dependency among the elderly, being overwhelming both for those who suffer from it and for their caregivers and relatives. It is estimated that between 5 and 8% of the population over 60 years of age will suffer from dementia at some point in time [2]. The increasing incidence of the disease and the lack of curative pharmacological treatments justify the demand for prevention strategies.

Evidence suggests that certain diets are associated with a lower incidence of neurodegenerative diseases, so maintaining a healthy diet may impact many risk factors for cognitive decline. A model to follow seems to be the Mediterranean diet [3]. The Mediterranean dietary pattern includes as distinctive characteristics, a daily consumption of vegetables, fruits, whole grains and healthy fats; the moderate intake of red wine and the use of extra virgin olive oil; all of them foods with a high content of phenolic compounds.

Phenolic compounds are a group of secondary plant metabolites, synthesized through the shikimate/phenylpropanoid and acetate/malonate pathways, characterized by having a structure with at least one phenol unit. Based on their chemical structures, they can be divided into different subgroups, such as phenolic acids, flavonoids, tannins, coumarins, lignans, quinones, stilbenes, and curcuminoids. Among them, flavonoids constitute one of the largest groups and are widely distributed in the human diet. Despite the great variety of existing flavonoids, their wide distribution and the important variations in their content, it is considered that only a limited number of these compounds are present in significant amounts in the foods that are commonly consumed in the diet. These include compounds derived from three anthocyanidins (cyanidin, delphinidin, malvidin), three flavan-3-ols (catechin, epicatechin, epigallocatechin), three flavonols (quercetin, kaempferol, myricetin), two flavanones (hesperetin, naringerin), two flavones ( apigenin, luteolin) and three chalcones [4].

During the last decade, there has been a growing interest in the possible cognitive benefits of consuming various subclasses of polyphenols, such as the flavanol and stilben family. These are present in a large number of plant-based foods, such as tea, cocoa, grapes, and red wine [5–7]. One concept to keep in mind is that polyphenol extracts used in supplementation and fortification may lack the synergistic effects on the health benefits of a diet naturally rich in polyphenols [8].

The mechanisms exerted by food polyphenols in their biological activity for the prevention and treatment of brain disorders are still under discussion, but it is believed that they may be due to direct mechanisms, possibly counteracting neuroinflammation and oxidative stress, thus improving the memory and/or cognitive function, or they may be due to indirect mechanisms that involve, among others, the modulation of the microbiota-gut-brain axis [9–11].

Neuroprotective benefits have been attributed to moderate consumption of grape polyphenols [12]. In fact, grapes are one of the richest sources of polyphenols. A serving of unpeeled grapes (200 g) could provide up to 72 mg of total phenols (Flame Seedless), including anthocyanins (cyanidin, malvidin, peonidin, petunidin, and delphinidin), the main phenolic compounds in red grapes; flavan-3-ols (catechin, epicatechin, procyanidins B1, B2 and C1, and gallocatechin), which are the most abundant phenolics in white varieties, and to a lesser extent derivatives of hydroxybenzoic and hydroxycinnamic acids, stilbenes (resveratrol) and flavonols (especially rutinoside and quercetin glycoside) present in both red and white grapes [13]. This diversity of compounds makes grapes, and especially red grapes, excellent candidates for testing the role of dietary polyphenols in health.

The consumption of raisins dates back to prehistoric times, in which the grapes were dried for storage and transport, and there is evidence of the early use of raisins as a food. In the Mediterranean region it has been a frequently consumed food and is one of the dry fruits that characterize the Mediterranean diet [14]. The phenolic profile of raisins differs from that of grapes, due to hydrolysis and oxidation processes that occur in these compounds.

Clinical research related to the possible health benefits of raisins has intensified over the past 10 years. Raisins have been reported to have a low to moderate glycemic index and a low insulin index [15]. In an intervention study with raisin ingestion for 12 weeks, a significant reduction in blood pressure and increased satiety was observed, through leptin and ghrelin, which have been related to a reduction in cholesterol values, from low density lipoproteins, triglycerides and oxidized fatty acids in serum, as well as proinflammatory cytokines [16]. Therefore, raisins could have an effect in significantly reducing the risk of developing diabetes or cardiovascular disease. However, no studies have been found in which the effect of raisins on cognitive impairment in older people has been studied. More research is required to establish the effects at the cognitive level and the molecular mechanisms by which these effects would occur.

## Methods/design

### Objectives

According to the background, the main objective of this study is to evaluate the effect of an intervention based on including 50 g of raisins in the diet daily for 6 months, on the improvement of cognitive performance, cardiovascular risk factors and markers of inflammation in a population of older adults without cognitive impairment.

### Design

This study will be a randomized controlled clinical trial of two parallel groups. Each subject included in the study will be randomly assigned to one of two study groups: control group (no supplement), intervention group (50 g of raisins daily). The duration of the intervention will be 6 months. Detailed in Fig. 1.

**Fig. 1 Fig1:**
[figure not shown]
Study flow-diagram

### Study population

The participants will be selected by consecutive sampling, in the Primary Care consultations of urban health centers in Salamanca and Zamora (Spain). Each Primary Care team (doctor or nurse), taking into account the inclusion and exclusion criteria, will propose the patients to participate in the study. In case they are interested in participating, they will collect their personal data and deliver it to the main researcher. Previously, the main researcher will give a clinical session with the Primary Care team to explain the characteristics of the research study. The study population will include a sample of 80 people.

### Inclusion criteria

People of both sexes over 70 years of age, Mini Mental State Examination (MMSE) score greater than or equal to 24 points, autonomous to attend the center where the study is carried out and sign the informed consent.

### Exclusion criteria

Coronary or cerebrovascular atherosclerotic disease, diabetes mellitus, heart failure grade II or higher, moderate or severe chronic obstructive pulmonary disease, advanced kidney or liver disease, severe mental illness, oncological disease under treatment diagnosed in the last 5 years or terminal condition, morbid obesity (BMI ≥ 40 kg/m2), intolerance and/or allergy to any of the components of grapes or any other circumstance at the discretion of the researchers.

### Sample size

The sample size was estimated taking into account the main variable of the study, the change in cognitive performance (categorical fluency). Accepting an alpha risk of 0.05 and a beta risk of 0.2 in a bilateral contrast, 40 subjects in the intervention group and 40 in the control group are needed to detect a difference equal to or greater than 2 points in the categorical fluency test. The common standard deviation is assumed to be 4.75 and a correlation coefficient between the initial and final measurement of 0.8. These estimates have been made based on contrasted data in the study by Garcia-Yu et al. [17]. Losses to follow-up of 10% have been estimated.

### Recruitment

The assignment of participants to the intervention group (IG) or control group (CG). The allocation sequence will be generated by an independent researcher using the Epidat 4.2 program (Department of Health, Government of Galicia, Spain), with a ratio of 1/1. The assignment will remain hidden until the participants are assigned to each group.

### Study variables

The main variable of the study will be the cognitive performance measured by several tests. The secondary variables will be body composition, blood pressure, heart rate, level of physical activity, quality of life, activities of daily living, energy and nutritional composition of the diet, markers of inflammation and other laboratory tests. clinical relevance.

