### Statistic analysis

The results will be expressed as the mean ± standard deviation in quantitative variables or by frequency distribution in the case of qualitative variables. Normality will be evaluated using the Kolmogorov–Smirnov Test. In cases where a normal distribution cannot be assumed, the corresponding non-parametric tests will be used. The chi square test will be used to analyze the association between independent qualitative variables and the McNemar test for paired samples. Using the Student's t-test (Mann–Whitney U) for independent samples, the means between two groups will be compared, evaluating the change within the same group with the Student's t-test for paired data (Wilcoxon's test). The relationship between quantitative variables will be analyzed using Pearson's correlation coefficient (Spearman's correlation coefficient). A multivariate analysis will be carried out using different multiple linear and logistic regression models to analyze the effect of adding 50 g of raisins to the usual diet on the improvement of cognitive performance, on the modification of weight and body composition, blood pressure, glycaemia, in the improvement of the quality of life and changes in the markers of inflammation.

In all cases, it will be adjusted taking into account the variables that may influence the result, such as sociodemographic variables, those related to lifestyles (physical activity and diet, smoking status), drug use, the presence of comorbidity or the basal BMI, among others. For bilateral hypothesis tests, an alpha risk of 0.05 is set as the limit of statistical significance. The statistical program will be SPSS, v.26.0.

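### The sample size section makes categorical fluency the one main variable, but the variables section makes it several unranked cognitive tests; the planned 80 participants fit only the first

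*Protocol article*

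**What the plan says.** Three places in the protocol article bear on what is primary.

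- **Sample size** speaks of "the main variable of the study, the change in cognitive performance (categorical fluency", which is one test. The effect size (2 points), standard deviation, correlation, alpha and power all refer to that test.
- **Study variables** states: "The main variable of the study will be the cognitive performance measured by several tests". The Methods part of the abstract lists the tests as "Mini-Mental State Examination test, Rey Auditory Verbal Learning Test, verbal fluency and montreal cognitive assessment (Moca". The subsections on cognitive evaluation describe the four in turn, without ranking them or combining them into one score.
- **Objectives**, repeated in the abstract's Background, frames the main objective as the effect of raisins "on the improvement of cognitive performance, cardiovascular risk factors and markers of inflammation". Study variables classes much of this differently: "The secondary variables will be body composition, blood pressure, heart rate, level of physical activity", and its list goes on to include markers of inflammation and other laboratory tests.

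**Statistic analysis** singles out no primary comparison. It sets one general threshold: "For bilateral hypothesis tests, an alpha risk of 0.05 is set as the limit of statistical significance".

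**The concern.** Sample size and Study variables use the same term, the main variable, for different things: one test in the first, an unranked group of tests in the second. A reader cannot tell which result decides whether the trial succeeded.

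If only fluency decides, the design is coherent. If any of several tests may decide, each at 0.05, the error rate is above 5% and the sample size was calculated for a different question.

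Two features of this trial make the point more than editorial. The Discussion says participants are not blinded, and it plans a first publication of primary results followed by another of secondary results. Which tests belong in the first paper depends on which section is followed. With the text as it stands, a favourable result on one of the four tests could be presented as primary, and readers could not tell whether it was chosen in advance.

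**Working it through.** **Inputs from Sample size:** difference 2 points; common SD 4.75; correlation between initial and final measurement 0.8; two-sided alpha 0.05; power 0.80; loss 10%. The 1:1 ratio is from Recruitment. The count of four cognitive tests is from the abstract and the subsections on cognitive evaluation.

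**Step 1: reproduce the stated 40 per group.**
- SD of the change = 4.75 × √(2 × (1 − 0.8)) = 4.75 × √0.4 = 3.004.
- n per arm = 2 × (1.960 + 0.842)² × 3.004² / 2² = 35.4, rounded up to 36.
- Allowing for 10% loss: 36 / 0.9 = 40. This matches the stated figure.
- Power with 36 completers per arm is 80.6% by the normal approximation and 79.5% by the non-central t distribution.

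Two other readings do not match. Using the raw SD of 4.75 gives 89 per arm, or 99 after loss. A baseline-adjusted analysis, with SD 4.75 × √(1 − 0.8²) = 2.85, gives 32, or 36 after loss. The calculation is therefore for one between-group comparison of change in fluency, at the full 0.05.

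**Step 2: error rate under each definition.**
- Fluency alone: 5%.
- Four tests, each at 0.05, success on any one, independent: 1 − 0.95⁴ = 18.5%.
- Four tests, equally correlated, by simulation of two-sided normal tests:

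| Assumed pairwise correlation | Chance of at least one false positive |
|---|---|
| 0 | 18.5% |
| 0.3 | about 17% |
| 0.5 | about 16% |
| 0.7 | about 13% |

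The article gives no correlations, so these values are assumptions. Four is a lower bound on the comparisons, because the Rey subsection describes several functions and does not choose one score. With five scores the independent figure is 1 − 0.95⁵ = 22.6%.

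**Step 3: does the sample size fit four primaries?** For illustration only, take a Bonferroni split, 0.05 / 4 = 0.0125, with the fluency assumptions unchanged.
- n per arm = 2 × (2.498 + 0.842)² × 3.004² / 2² = 50.3, rounded up to 51.
- Allowing for loss: 51 / 0.9 = 56.7, rounded up to 57 per arm, against the planned 40.
- At the planned 36 completers per arm, power for the 2-point fluency difference would be 63% by the normal approximation and 60% by the non-central t.

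The article does not propose this design. The calculation shows only that the planned number does not support it.

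**The case against.** **The two sections can be reconciled.** Both name cognitive performance as the domain. Sample size then specifies one test within it and is the only place with an effect size and power. On that reading fluency is the sole primary, alpha is 5%, and the stated number is correct. This is plausible, and it means the inflation is conditional. It does not remove the contradiction: Study variables is where outcomes are classified, it omits the specification, and nothing says that Sample size takes precedence.

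**Multiplicity rules may sit in a document not shown.** This stands. The lack of an adjustment method is not the finding. A separate analysis plan could choose one reading, but these two sections would still disagree about the primary outcome.

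**Stronger readings that the article does not support:**
- *Three rival primary targets, with success claimable on any of them.* A reader might infer this from Objectives. That sentence states an aim, not a main variable, and Study variables lists blood pressure, heart rate, body composition and inflammation markers as secondary.
- *An error rate near 64%.* This would come from counting about 20 variables as primary: 1 − 0.95²⁰ = 64%. The count is an assumption, it promotes secondary variables, and it treats related measures as independent. At an assumed correlation of 0.7 the figure would be about 29%.
- *The 5% rate is simply not held.* No section states that one significant test is enough, so this follows only under the reading set out in Step 2.
- *MMSE has little room to improve because entry requires at least 24 points.* The article gives no baseline MMSE distribution, and the remark has no bearing on which outcome is primary.

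**Conclusion.** The point holds as a contradiction over the primary outcome. Sample size names one test; Study variables names several without ranking them. The stated 40 per group is right for the first definition and was not calculated for the second.

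Its size depends on which section governs. Under Sample size the error rate is 5%. Under Study variables, with success on any one of four tests at 0.05, it is 18.5% if the tests are independent and about 13% if they are correlated at 0.7. That range rests on the assumed correlations, on a count of four comparisons, and on an any-one-test rule that the article neither states nor excludes.

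The breadth of the main objective is a second and lesser inconsistency, because Study variables already places most of those measures among the secondary variables.

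The correction should be made before results are known, since it settles which result the primary publication will report.

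**What to change.** - **Study variables:** name the between-group difference in 6-month change in categorical fluency as the single primary outcome, matching Sample size. List MMSE, Rey and MoCA as secondary.
- **Objectives and the abstract's Background:** reword the main objective so that cardiovascular risk factors and inflammation markers become secondary objectives.

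This costs wording only. The 40 per group stands and the primary comparison keeps its 5% error rate. The small downside is that a significant MMSE, Rey or MoCA result can no longer be presented as the primary finding.

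If the sponsor prefers several primary tests, the protocol must name each score, state how the error rate is shared among them, and recalculate the sample size. Step 3 indicates the scale for a Bonferroni split across four tests: 57 per arm instead of 40.

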### Methods used in the evaluation of cognitive performance

#### Mini Mental State Examination (MMSE) [18]

This test will evaluate temporal and spatial orientation, fixation, attention and calculation capacity, memory, nomination, repetition, comprehension, reading, writing and the drawing. The score ranges between 0 and 30 points, considering that a score greater than 24 represents normal cognitive performance.

#### Rey Auditory Verbal Learning Test [19]

This test analyzes memory retention and immediate recall, verbal learning of a list of words, and the subject's retention capacity after a non-amnestic interference task. The validated version in Spanish will be used.

#### Verbal fluency [20]

It is a categorical fluency test in which the participant is asked to list animals for one minute.

#### Montreal cognitive assessment (Moca*) *[21]

With this cognitive battery, short-term memory, visuospatial capacity, executive functions, attention, concentration, working memory, language and temporal-spatial orientation will be evaluated. The validated version in Spanish will be used. The total score is 30 points, with ≥ 26 points being an indicator of normality. If the subject has less than 12 years of schooling, a point will be added to the score obtained when taking the test.

### Methods used in the evaluation of secondary variables

#### International Physical Activity Questionnaire (IPAQ) [22]

The short version will be used, which consists of 7 questions about the frequency, duration and intensity of the activity (moderate and intense) carried out during the last 7 days. It also evaluates the time spent walking and the time spent sitting.

#### Quality of life instrument of the World Health Organization (WHOQOL) called WHOQOL-AGE [23]

Which has been specially adapted to the elderly population. This short version has 13 of the 100 questions of the original version and has been validated in populations older than 50 years. Results can range from 0 (lowest quality of life) to 100 (highest quality of life).

#### EuroQol 5-D Questionnaire [24]

It will be used to assess health-related quality of life. We will use an adapted version of this questionnaire that has been validated for the Spanish population. This questionnaire consists of three elements: the assessment of the individual's health status in severity levels by dimensions (mobility, self-care, usual activities, pain/discomfort and anxiety/depression), the assessment of their health status on a visual analog scale and, finally, an index of social values obtained for each state of health generated by the instrument.

